### Recruitment

**
*GP practice recruitment*
**

General practices affiliated with the HRB Primary Care Clinical Trials Network Ireland, who have previously expressed an interest in hypertension research and are within the catchment area of the biochemistry laboratory at University Hospital Galway, will be invited to participate. A detailed practice information sheet will be provided (see
*Extended data*). If invited practices express interest in taking part, research staff on the project will follow up with a telephone call to provide further details about the study. All participating practices will be offered €100 per recruited patient participant to cover the additional administration costs, as well as a right to keep a 24-hour ambulatory blood pressure monitor (ABPM) after the study has ended.

**
*Patient participant recruitment*
**

The practice administrator/manager, supported by the research team, will search the practice records using the inclusion and exclusion criteria to identify eligible patient participants.

Once identified, the practice will post a letter of invitation and information sheet to a random selection of 20 patients from each practice (this is based on a 50% recruitment rate as seen in a previous feasibility study
^
24
^). The random selection will be facilitated using random.org. These patients will be asked to contact the research team if interested in taking part. If there is no response after 10 days, the practice will contact eligible patients by phone and explain the information in the letters and offer an opportunity to ask questions. If the target of 10 participants is not met at that point, another 10- 20 letters will be sent out, dependent on the response to date. This will continue until the target is met. All interested patients will receive a consent form in the post, which they will be asked to return to the team before the trial begins. All patient participants will be offered a €40 multi-store voucher to cover costs associated with their participation (e.g., travel to the practice for study visits).

### Randomisation procedures

After all participants have been recruited, three GP practices will be randomised to the MIAMI intervention and three will be randomised to the usual care control. The code to generate the randomisation plan will be written in
R (using a reproducible random generation seed) and implemented by an independent statistician.

### Intervention procedures

The MIAMI intervention will be delivered at a minimum of one GP appointment during a three-month period. The intervention arm and control arm are described below.

**
*MIAMI intervention arm*
**

The MIAMI intervention is a structured set of supports for GPs and patients with hypertension to facilitate adequate information exchange within consultations about long-term antihypertensive medication use and adherence skill development. Full details are in
Table 2. It will include the following, where indicated:

Patients

Wearing an ABPM and providing a urine sample for a chemical urine test of adherence.Filling out a brief ‘pre-consultation plan’ before a GP consultation.

GPs

Training in how to structure a consultation around adherence issues. This will be provided through online videos and will take a maximum of 30 minutes.A booklet with key takeaways from training videos and current guidance around blood pressure medication prescribing (from the European Society of Hypertension
^
3
^ and American College of Cardiology
^
25
^)A drop down menu on GP software which will provide a reminder of consultation guide and a list of resources that can be recommended to the patient (e.g., medication reminders - dontforget.ie and BP information - croi.ie/health/heart-conditions/high-blood-pressure/)

The patient flow through the intervention arm can be seen in
Figure 1.

**Figure 1. f1:**
[figure not shown]
Patient flow through MIAMI intervention arm.

**
*Control group*
**

Participants in the control group will receive usual care. This would involve visits by patients to GPs where blood pressure would be measured manually via office-based sphygmomanometer or automated blood pressure device and management decision on how best to proceed would stem from this meeting, which is typically scheduled every 3-4 months for patients over 65. Blood pressure may also be assessed via out of office assessment if manual readings are high. Previous research has demonstrated typical appointments between hypertensive patient and their GP does not often involve structured discussions about adherence
^
11,
12
^.

Patient flow through the control arm can be seen in
Figure 2.

**Figure 2. f2:**
[figure not shown]
Patient flow through the control arm.

### Data collection

**
*Participant quantitative data collection*
**

*Patients*

Patient data collection will occur at two time points during the trial. These include:

T1) Baseline

T2) Follow up (3 months later)

Self-report questionnaires for T1 and T2 will be administered to participants at the GP practice. The questionnaire will be paper based and will include questions on demographics, outcome measures, and resource use (for health economic analysis). For the blood pressure measurement outcomes, participants will be given an ABPM at T1 and T2. For the objective adherence outcome, participants will provide a urine sample which will undergo chemical adherence testing
^
6
^. All other quantitative data will be taken from practice records by the lead researcher.

Please see
Table 3 for description of outcome measures.

**Table 3. T3:** Patient outcome measures.

Outcome	Measurement	When	Method of capture
Systolic BP	24 hour ABPM (average day reading)	T1 & T2	Researcher entry
Diastolic BP	24 hour ABPM (average day reading)	T1 & T2	Researcher entry
BP control	24 hour ABPM (readings above or below 140/90 mmHg)	T1 & T2	Researcher entry
Medication adherence	Urine screen (Adherence ratio *)	(T1) & T2 **	Chart review
Medication adherence	Prescription refill record	T1 & T2	Chart review
Medication adherence	Medication Adherence Report Scale ^ 27 ^	T1 & T2	Patient self- report
Beliefs about medication	Beliefs about Medicines Questionnaire ^ 28 ^ Illness Perceptions Questionnaire– Revised (‘treatment control’ & ‘consequences’ items) ^ 29 ^	T1 & T2	Patient self- report
Habit strength	Self-Report Behavioural Automaticity Index ^ 30 ^	T1 & T2	Patient self-report
Patient assessment of care	Patient Assessment of Chronic Illness Care ^ 31 ^ ***	T1 & T2	Patient self-report
Medication prescription/pill burden	Type and dosage	T1 & T2	Chart review
Health related QoL	EuroQoL-5D-5L	T1 & T2	Patient self- report
Wellbeing	ICECAP-O	T1 & T2	Patient self- report

**
*Ratios are calculated for each patient – based on the medications that could be detected – by dividing the total number of antihypertensive medications detected in spot urine into the total number of detectable antihypertensive medications prescribed, whereby total non-adherence was equal to 0 and perfect adherence was equal to 1*
*
*This outcome will not be captured at baseline in the control arm, due to a concern around the provision of clinical information to GPs without guidance on management. It will be captured at follow up in the control arm, as all GPs will have access to intervention materials at study end.*

**** Four of the five subscales - recent psychometric evaluation evidence that indicates that ‘Follow-up/Coordination’ sub-scale and item 10 is the least psychometrically robust and that a 14-item measure with an underlying four factor structure provides more psychometrically robust measurement than the original 20 item scale with a 5 factor structure
^
32
^
*

**
*GPs*
**

This data will be collected at T1 only. A questionnaire will gather demographic and personal information including: length of time working in primary care, employment basis (full-time, part-time, and other), practice location (urban/rural) and practice size.

**
*Feasibility and acceptability data*
**

The following will also be measured:

1.Recruitment of GP practices will be assessed by documenting the number of invitations sent, the number of refusals and number of acceptances.2.Recruitment of patients will be assessed by documenting the number of invitations sent, the number of initial responses, the number of follow-up phone-calls required, the number of refusals and the number of acceptances.3.Attrition of participants will be documented at every time-point.4.Levels of missing data in returned questionnaires will be reported.5.The comprehensibility and acceptability of all questionnaires will be measured by asking participants how the questionnaires might be improved, and how long they took to complete.

**
*Qualitative evaluation of feasibility and acceptability*
**

A descriptive qualitative approach
^
26
^ will be used to explore the perceptions and experiences of people with hypertension (n = 6) and GPs (n = 3) of participating in the MIAMI study and their views as to the acceptability of the intervention. In the intervention arm, six patient participants will be invited to participate in one-to-one interviews at month 1 (post first GP visit) and again at month 3 (post follow up visit). These longitudinal interviews will give an insight into participants’ views and changes in perceptions as they progress through the study. In addition, GPs delivering the intervention (n = 3) will be interviewed at month 3. These interviews will focus on their experiences of delivering the intervention and their views on its acceptability and feasibility in practice.

Patient participants (n = 6) and GPs (n = 3) in the control arm will be invited to one-to-one interviews at month 3. The focus of these interviews will be to acceptability of taking part in a pilot RCT in the control arm. The interview guides can be seen as
*Extended data*. Thematic analysis as outlined by Braun & Clarke
^
33
^ will be used to analyse the data. Rigour will be maintained by adhering to the criteria described by Lincoln & Guba
^
34
^ and the computer software package
NVivo will be used to assist the analysis process.

**
*Fidelity*
**

Fidelity assessment will provide valuable information on the feasibility of intervention implementation, as well as information on the acceptability and usefulness of the fidelity assessment procedures which may require adaptation for the definitive RCT.

*MIAMI intervention training fidelity*

Attendance by GPs in each practice at the initial training method will be recorded. Analytics such as the number of clicks and time spent on each page will also be available from the GP training website.

Analytics such as number of clicks and time spent on each page will be available from the GP training website.

*MIAMI intervention delivery fidelity*

A checklist embedded as a ‘Drop-Down Menu’ in the Socrates practice software system will be developed for the distinct components in the MIAMI intervention. This checklist will be completed by GP participants during each consultation and subsequently reviewed by the research team.

Fidelity will also be explored in the qualitative interviews with patient and GP participants.

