### Inclusion and exclusion criteria

Please see
Table 1 for inclusion and exclusion criteria.

**Table 1. T1:** Inclusion and exclusion criteria.

Inclusion criteria for GP practices	Inclusion criteria for GP participants	Inclusion criteria for patient participants
• Within catchment area of biochemistry lab at University Hospital Galway • Use Socrates software system	• Doctors who are providing patient care in the practice	• A confirmed diagnosis of hypertension • Participants must be over the age of 65 • Participants must be on two or more anti- hypertensive medications • Participants must not be achieving recommended blood pressure levels, i.e., clinic readings are higher than 140/90 mmHg or day ABPM 135/ 85 mmHg • In the judgement of the GP regarding a change in medication, the balance of risk / benefit lies in favour of benefit.

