### Sample size calculations

As this is a pilot study, a formal sample size calculation is not warranted. One of the aims of the study is to generate the estimates needed for a sample size calculation for a future definitive trial. In order to generate the reliable estimates needed, it is proposed that six clusters (three in the intervention arm, three in the control arm) each containing 10 patient participants are recruited. Each cluster will be an independent GP practice, meeting the inclusion criteria laid out in
Table 1. The number of clusters chosen is governed by pragmatism and to provide a representative sample (using best judgement) of the diversity in the population of clusters from which data in the definitive trial will be sampled. 

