### Statistical analysis

Suitable summary statistics (e.g., mean, standard deviation, and frequency) will be provided for the main outcomes. These summary statistics will guide the sample size calculation needed for the future definitive two arm cluster RCT
^
37,
38
^.

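### Table 3 scores BP control from ABPM at 140/90 mmHg, while Table 1 sets the daytime ABPM limit at 135/85 mmHg, so a participant can be uncontrolled by one table and controlled by the other

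*Protocol article*

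**What the plan says.** In the protocol article, Inclusion and exclusion criteria, Table 1, a patient is not at the recommended BP if "clinic readings are higher than 140/90 mmHg or day ABPM 135/ 85 mmHg". This gives two limits, one for each way of measuring.

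Under Data collection, ABPM is the only device named for the BP outcomes: "For the blood pressure measurement outcomes, participants will be given an ABPM at T1 and T2". Table 3 then has three BP rows. The systolic and diastolic rows both use "24 hour ABPM (average day reading", in parentheses. The BP control row uses "24 hour ABPM (readings above or below 140/90 mmHg", also in parentheses. It carries the figure that Table 1 gives for clinic readings and does not name the ABPM summary to be classified.

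Statistical analysis promises summary statistics, frequencies among them, for the main outcomes, and adds: "These summary statistics will guide the sample size calculation needed for the future definitive two arm cluster RCT". It does not list the main outcomes. Sample size calculations says: "As this is a pilot study, a formal sample size calculation is not warranted".

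**The concern.** The trial enrols people because their BP is above target, and one of its outcomes is whether BP is at target. The two definitions should agree for the same device, and here they differ by 5 mmHg on both components. The article gives no reason, such as a deliberately looser target for the outcome.

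Two things are at stake. First, the reported control proportion would include people who still exceed the ABPM limit by which the trial calls BP uncontrolled. Some could count as controlled at baseline and so have no room to become controlled by T2. Second, the aims include assessing the outcome measures and informing the size of a definitive trial. An outcome whose threshold disagrees with the entry criterion is a weak basis for either, and the mismatch could be carried into the full trial.

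**Working it through.** **1. Inputs.** From Table 1: clinic limit 140/90, daytime ABPM limit 135/85. From Table 3: ABPM control limit 140/90; systolic and diastolic outcomes are average day ABPM readings. The article gives no mean, SD or control rate for ABPM and no figure for this outcome, so there is no stated result to reproduce.

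**2. Both rules on the same daytime average.** I read a pair as above the limit if either component is above it, and I assume the control row classifies the daytime average, as the adjacent rows do.

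| Daytime ABPM average | Table 1 ABPM limit | Table 3 control row |
|---|---|---|
| 134/84 | at target | controlled |
| 136/80 | not at target | controlled |
| 138/84 | not at target | controlled |
| 134/88 | not at target | controlled |
| 137/87 | not at target | controlled |
| 141/80 | not at target | not controlled |
| 130/91 | not at target | not controlled |

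The tables disagree where systolic is above 135 or diastolic above 85, while systolic is at most 140 and diastolic at most 90. The conflict does not depend on how the slash is read. At 137/87 both components are above 135/85 and neither is above 140/90.

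**3. Direction.** Every reading with systolic ≤135 and diastolic ≤85 also has systolic ≤140 and diastolic ≤90. So on the same data, P(controlled at 140/90) ≥ P(controlled at 135/85), in each arm and at each time point. This needs no distribution.

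**4. Size, for illustration only.** Assume that daytime averages are bivariate normal. Control at limit (a, b) is P(SBP ≤ a and DBP ≤ b).

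With mean 142/80, SD 12/9 and correlation 0.5:
- at 140/90: 0.415
- at 135/85: 0.252
- difference: 0.415 − 0.252 = 0.163, or 30 × 0.163 ≈ 5 of the 30 participants planned per arm (3 practices × 10)
- share of those above 135/85 who are scored controlled: 0.163 / (1 − 0.252) = 0.22

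Varying the assumptions (systolic mean 135 to 150, SD 10 to 15; diastolic mean 78, SD 9; correlation 0.5):

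| Systolic mean, SD | Control at 140/90 | Control at 135/85 | Difference | Difference / (1 − control at 135/85) |
|---|---|---|---|---|
| 135, 10 | 0.662 | 0.451 | 0.211 | 0.384 |
| 135, 15 | 0.607 | 0.451 | 0.156 | 0.284 |
| 150, 10 | 0.157 | 0.065 | 0.092 | 0.098 |
| 150, 15 | 0.249 | 0.152 | 0.097 | 0.114 |

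Over this range the control proportion moves by about 9 to 21 percentage points. About 10% to 38% of those above the Table 1 ABPM limit would be scored controlled. Counting only people with systolic between 135 and 140 would not give the reclassified share: 137/94 is uncontrolled under both rules, while 132/87 changes category on diastolic alone.

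**5. After reconciliation.** With one ABPM limit in both tables, the zone of disagreement in step 2 is empty.

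**The case against.** The strongest reply is that little hangs on this row. The study is a feasibility pilot with descriptive analysis and no formal sample size calculation. BP control is in none of the five stop/go criteria in Table 4. Table 3 also collects average day systolic and diastolic readings, so control can be recomputed later at any limit. All of this stands, and it keeps the severity at moderate. It does not remove the contradiction, and choosing the limit after seeing the data would be a post hoc choice.

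Three stronger readings are tempting and are not supported.

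- *Participants are admitted and scored controlled on one and the same reading.* Patients are identified by searching practice records, and the outcome ABPM is worn at T1. Nothing says that the qualifying reading is the T1 ABPM. Patients may also qualify on a clinic reading alone, so some could be below either ABPM limit at T1, and aligning the limits would not change that.
- *The definitive sample size will be wrong.* The article does not say that BP control is one of the main outcomes or that its proportion will be used. A proportion at 140/90 would mislead only if it were used for an endpoint with a different limit.
- *The comparison between arms is biased in a known direction.* The same limit applies to both arms. The effect on the difference between them depends on distributions that the article does not give.

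It may also be said that the choice of ABPM summary belongs in a full protocol or SAP, neither of which is shown. That is fair, and the missing word about daytime averages adds nothing to the severity. The threshold is different: the article states it, and it conflicts with Table 1.

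**Conclusion.** The inconsistency is real and follows from the article's own two tables. A daytime ABPM average above 135/85 but not above 140/90 is off target under Table 1 and controlled under Table 3. The direction is certain if the control row is applied to the daytime average: relative to Table 1's ABPM limit, reported control can only stay the same or rise. The size is not derivable from the article. About 41.5% against 25% is an illustration under assumed values, and the wider range in the working rests on assumptions too.

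Severity is moderate. The consequence for the definitive design is a possibility, conditional on this proportion being used for the sample size. Nothing here says which limit is clinically right; the point is that the two tables must be reconciled.

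**What to change.** Reconcile Tables 1 and 3 before outcome data are examined. Either:

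- define BP control in Table 3 from the average day ABPM reading, using the same daytime ABPM limit that the trial uses for eligibility; or
- keep the different limit, state the reason for it, and report control at both limits.

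In either case, name the average day reading in the control row and say how the two components combine and how a value exactly at the limit is scored. If a control proportion is carried into the definitive sample size, state the limit with it.

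The cost is one line in Table 3 and a line of analysis code. The average day systolic and diastolic values are already collected at T1 and T2, so no new data are needed. Control reported at the eligibility limit will be no higher than at 140/90. Adding a separate control outcome from clinic readings is not part of this fix, because Table 3 lists no clinic BP.

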### Health economic analysis

A pilot health economic assessment of the MIAMI intervention will be conducted to provide preliminary cost effectiveness estimates and to inform the design of a future definitive economic evaluation. A healthcare perspective will be adopted with respect to costing. Data collection tools will be developed for the purposes of measuring data on resource use over the trial follow-up period. An exploratory process will be conducted to identify the resource use and costs associated with the delivery of the MIAMI intervention. Unit costs will be identified and applied to convert data on resource use to costs. For the pilot cost utility analysis, Quality Adjusted Life Years (QALYs) will be estimated using data collected using the EuroQol EQ-5D-5L instrument
^
35
^ and the ICECAP-O instrument
^
36
^ at baseline and follow up. A preliminary analysis will be undertaken to provide information on the incremental costs and incremental effects of the MIAMI intervention relative to the usual care control, and a range of techniques will be employed to address uncertainty. The pilot analysis is designed to determine the feasibility of the approaches adopted and not cost effectiveness.

### Statistical analysis

Suitable summary statistics (e.g., mean, standard deviation, and frequency) will be provided for the main outcomes. These summary statistics will guide the sample size calculation needed for the future definitive two arm cluster RCT
^
37,
38
^.

### Progression to a full RCT

The following pre-defined stop/go criteria in
Table 4 will be used to inform the decision on whether to proceed to a full trial.

**Table 4. T4:** Stop/go criteria.

	Go – proceed with full RCT	Amend – proceed to full RCT with changes	Stop – do not proceed unless major changes are possible
1. Feasibility of practice recruitment Can 6 practices be recruited to take part in 3 months?	If ≥5 practices are recruited to take part in 3 months	If ≥5 practices are recruited, but it takes longer than predicted (e.g. 3–6 months)	Unable to recruit at least 4 practices.
2. Feasibility of patient recruitment Can 10 patients per practice (total n = 60) be recruited?	If 8–10 patients are recruited in one month per practice: total of 60 (100%)	If 6-7 patients are recruited in one month per practice: total of 36–60 (60% to ≤100%)	If <6 patients are recruited in one month per practice: total of ≤36 (<60%)
3. Feasibility of practice retention Can all 6 practices be retained in the study until completion?	≥5 retained	≥4 retained	≤3 retained
4. Feasibility of patient retention * Can at least 90% of recruited patients be retained in the study until completion?	>9 patients (90%) retained	7–8 patients (70-80%) retained	<7 patients (<70%) retained
5. Intervention feasibility	Delivery of intervention judged strongly feasible by qualitative data	Delivery of intervention judged mainly feasible by qualitative data	Delivery of intervention judged problematic by qualitative data

**Retention will be defined as availability of final outcome measures*.

The Decision-making after Pilot and feasibility Trials (ADePT) process involves examining 14 methodological issues that are pertinent to feasibility research. We will use this process, as well as the progression criteria, findings from the qualitative research, and discussions with the study research team, Trial Management Group, Trial Steering Committee and the public and patient involvement (PPI) panel to make a decision on whether to progress to full RCT.

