## Study status

Five GPs practices have been recruited. Patient participant recruitment began in November 2022.

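### Table 4, criterion 2: the per-practice bands and the totals disagree, five practices (a criterion 1 Go) cannot reach the criterion 2 Go total, and four practices has no criterion 1 verdict

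*Protocol article*

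**What the plan says.** The section on sample size plans for "six clusters (three in the intervention arm, three in the control arm) each containing 10 patient participants are recruited", that is 60 patients. Table 4, in the section on progression to a full RCT, repeats this target as the question for criterion 2: "Can 10 patients per practice (total n = 60) be recruited".

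The three criterion 2 cells are as follows (each bracket holds a percentage of 60):

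- Go: "If 8–10 patients are recruited in one month per practice: total of 60 (100" per cent)
- Amend: "If 6-7 patients are recruited in one month per practice: total of 36–60 (60% to ≤100" per cent)
- Stop: "If <6 patients are recruited in one month per practice: total of ≤36 (<60" per cent)

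Criterion 1, on practices, is Go as follows: "If ≥5 practices are recruited to take part in 3 months". Amend also needs at least five practices, but over a longer time. Stop is "Unable to recruit at least 4 practices".

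The study status section reports: "Five GPs practices have been recruited". Nothing in the article says whether the per-practice count or the total governs criterion 2.

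**The concern.** A three-way progression rule needs bands that do not overlap and that leave no outcome out. Each criterion 2 cell joins a per-practice range to a total that does not follow from it, so one recruitment result can earn two different verdicts. The two recruitment criteria are also built on different numbers of practices: criterion 1 accepts five, while the criterion 2 totals presume six.

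Feasibility of a definitive trial is a stated aim of the pilot, and feasibility of recruitment is its second objective. The criteria are presented as set in advance. If the verdict depends on which half of a cell is read once the counts are known, that protection is lost for the recruitment rows.

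**Working it through.** **Inputs.** Six practices and 10 patients each (sample size section; criterion 2 question). Per-practice bands of 8–10, 6–7 and below 6, with totals of 60, 36–60 and at most 36 (criterion 2). Practice thresholds of at least five for Go and Amend, and fewer than four for Stop (criterion 1). Five practices recruited (study status).

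**The plan's own figures first.** 6 × 10 = 60, so the target reproduces. 6 × 6 = 36 and 36/60 = 60%, so the lower edge of Amend reproduces. The other edges do not.

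**Totals implied by the per-practice bands** (practices × patients per practice, as a share of 60):

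| Band | Six practices | Five practices | Total printed |
|---|---|---|---|
| Go, 8–10 | 48–60 (80–100%) | 40–50 (67–83%) | 60 (100%) |
| Amend, 6–7 | 36–42 (60–70%) | 30–35 (50–58%) | 36–60 (60–100%) |
| Stop, 5 or fewer | 0–30 (≤50%) | 0–25 (≤42%) | ≤36 (<60%) |

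**Verdicts when every practice recruits the same number:**

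| Each practice | Per-practice verdict | Six practices: total and its verdict | Five practices: total and its verdict |
|---|---|---|---|
| 5 | Stop | 30, Stop | 25, Stop |
| 6 | Amend | 36, Amend and Stop | 30, Stop |
| 7 | Amend | 42, Amend | 35, Stop |
| 8 | Go | 48, Amend | 40, Amend |
| 9 | Go | 54, Amend | 45, Amend |
| 10 | Go | 60, Go and Amend | 50, Amend |

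With six practices, 7 is the only count from 6 to 10 at which both halves give the same single verdict. With five practices there is none.

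**The edge at 36.** 36/60 is exactly 60%. It satisfies the count in the Stop cell but not the percentage in that cell, and it also satisfies Amend.

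**Criterion 1 against criterion 2.** Five practices at target give 5 × 10 = 50, and 50/60 = 83%. To reach 60 they would need 60/5 = 12 each, above both the target and the top of the Go range.

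**Criterion 1 alone.** Five or six practices: Go or Amend, according to time taken. Three or fewer: Stop. Exactly four: neither Go nor Amend (both need five), and not Stop (four have been recruited). This is a gap in the bands, not an arithmetic error. Criterion 3, on practice retention, does place four under Amend.

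**The case against.** The best defence is that each cell holds two different quantities: a first-month pace and, after the colon, an eventual total. The recruitment section supports this, since further letters go out until the target of 10 is met. Amend then makes sense as a start of 6–7 per practice (at least 36) that may climb to 60, and a total of 60 is assigned to Go or Amend by pace.

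This reading removes some overlaps but leaves gaps. A start of 8–10 per practice that ends at 48–59 is neither Go (not 60) nor Amend (not 6–7). A start below 6 that ends at 37–60 has no verdict either. The clash in the Stop cell at 36 remains, and so does the unreachable Go total for five practices.

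Several stronger readings are tempting, and the article does not support them:

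- A reader might infer that any total from 48 to 59 is Go per practice. It need not be: 10 + 10 + 10 + 10 + 10 + 3 = 53 includes a practice in the Stop range. The contradiction is certain only where every practice has 8–10.
- A reader might infer that the conflict covers the likeliest results. The article gives no distribution of recruitment.
- A reader might take five practices as final. The status line is a snapshot and does not say that practice recruitment has closed.
- A reader might see a further gap for practice recruitment beyond six months. The 3–6 months in the Amend cell is only an example of taking longer than predicted.
- A reader might treat Table 4 as an automatic rule. It informs a decision that also draws on the ADePT process, the qualitative findings, the trial committees and the PPI panel.

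That last point stands and limits the consequence. Amend also still proceeds to a full trial, with changes. It does not make the printed bands consistent.

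**Conclusion.** Wrong as written, of moderate severity. The two halves of criterion 2 give different verdicts for six practices at 8 or 9 each (48 or 54) and for five practices at any common count from 6 to 10. The totals overlap at 60 (Go and Amend) and at 36 (Amend and Stop). A criterion 1 Go with five practices caps criterion 2 at 50/60 (83%), short of its Go total. Exactly four practices has no criterion 1 verdict.

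The cap assumes that no practice exceeds its target of 10. The tabulated conflicts assume equal recruitment across practices. The clashes at 36 and 60 and the gap at four practices need neither assumption. No estimate or test in the pilot is affected; what suffers is the clarity of the pre-set progression thresholds.

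**What to change.** Before the progression data are reviewed:

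1. State one governing scale for criterion 2, as a percentage of 10 × practices recruited, with exclusive and exhaustive bands, and say whether it is counted at one month or at the end of recruitment.
2. If the per-practice limits govern, the bands become Go at 80% or more, Amend from 60% to below 80%, and Stop below 60%. With six practices that is 48 or more, 36–47, and 35 or fewer of 60. With five it is 40 or more, 30–39, and 29 or fewer of 50. The team must confirm that this replaces the printed 100% Go total, because it is a choice between two stated thresholds and not just a correction of wording.
3. At minimum, change the Stop total to below 36 (<60%) and take 60 out of the Amend range. This removes the two overlaps in the totals but leaves the per-practice and five-practice conflicts.
4. Give exactly four practices a verdict in criterion 1, for example Amend, as in criterion 3.

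The cost is rewording two table rows, with no extra data. The downside is that the Go threshold will differ from one of the two now printed. Patient recruitment had already begun, so the change should be dated and explained.
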